## Abstract

**Background:**

Recent meta-analyses and randomized studies have shown that among patients with acute ischemic stroke undergoing endovascular thrombectomy, general anesthesia with mechanical ventilation is associated with better functional status compared to local anesthesia and sedation, and they recommend its use. But once the procedure is completed, when is the optimal moment for extubation? Currently, there are no guidelines recommending the optimal moment for extubation. Prolonged mechanical ventilation time could potentially be linked to increased complications such as pneumonia or disturbances in cerebral blood flow due to the vasodilatation produced by most anesthetic drugs. However, premature extubation in a patient who has suffered a stroke could led to complications such as agitation, disorientation, abolished reflexes, sudden fluctuations in blood pressure, alterations in cerebral blood flow, respiratory distress, bronchial aspiration, and the need for reintubation. We therefore designed a randomized study hypothesizing that early compared with delayed extubation is associated with a better functional outcome 3 months after endovascular thrombectomy treatment under general anesthesia for acute ischemic stroke.

**Methods:**

This investigator-initiated, single-center, prospective, parallel, evaluated blinded, superiority, randomized controlled trial will include 178 patients with a proximal occlusion of the anterior circulation treated with successful endovascular thrombectomy (TICI 2b-3) under general anesthesia. Patients will be randomly allocated to receive early (< 6 h) or delayed (6–12 h) extubation after the procedure. The primary outcome measure is functional independence (mRS of 0–2) at 90 days, measured with the modified Rankin Score (mRS), ranging from 0 (no symptoms) to 6 (death).

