### Sample size {14}

We aim to compare neurological functional status at 90 days according to the modified Rankin scale (mRS), of patients with stroke who underwent endovascular thrombectomy with satisfactory results and who underwent early extubation (< 6 h) compared to delayed extubation (6–12 h). Efficacy will be assessed with the proportion of patients with functional independence (mRS scale ≤ 2).

A previous observational study [20] reported that 55.5% of patients achieved an mRS score of ≤ 2 after receiving early extubation (mechanical ventilation for less than 6 h), compared to 33.9% when extubation was delayed (mechanical ventilation for more than 6 h). In present trial, we hypothesize that early extubation, compared with delayed extubation, is associated with a better functional outcome 3 months after endovascular thrombectomy under general anesthesia for acute ischemic stroke. We have decided to set the level of significance at 5% (*α* = 0.05), with a power of 80% (*β* = 0.80), and to use a bilateral test (c = 2). We will work with two independent samples and both groups will be balanced (w1 = 0.5). Considering an expected percentage of losses is 5.00%, it would be necessary to include 87 individuals in each group, totaling 174 patients in the study. Depending on the course of the study, an interim analysis will be conducted when 70% of the recruited sample is reached, if deemed appropriate by the research team.We hypothesized that early compared with delayed extubation is associated with a better functional outcome 3 months after endovascular thrombectomy treatment under general anesthesia for acute ischemic stroke.

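### The Abstract gives a target of 178 patients and the sample size section gives 174; the article should state one total (minor)

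*Protocol article*

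**What the plan says.** The Methods paragraph of the Abstract says the "randomized controlled trial will include 178 patients with a proximal occlusion of the anterior circulation". Section {14} (Sample size) says "it would be necessary to include 87 individuals in each group, totaling 174 patients in the study".

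Section {14} gives its inputs. An earlier observational study "reported that 55.5% of patients achieved an mRS score of ≤ 2 after receiving early extubation", "compared to 33.9% when extubation was delayed (mechanical ventilation for more than 6 h"). The significance level is 5% with a two-sided test, power is 80%, allocation is equal, and 5% losses are expected. The total of 174 already contains the allowance for losses.

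Sections {14} and {21b} place an interim look at 70% of the sample recruited and leave it to the research team to decide whether to hold it. Neither section gives a patient count for that look. Section {15} reports 70 patients randomised by February 2024.

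**The concern.** The two statements are current text about the same quantity and differ by 4 patients. The article does not explain the difference or rank one total above the other. As section {14} already includes losses, 178 cannot be read as 174 plus attrition.

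The planned total tells the team when to stop enrolling. With two published totals, stopping at either could be described as following the plan. This matters somewhat more here than in a trial with independent oversight: the oversight section says there is no data and safety monitoring board, and two investigators manage data quality and the statistical analysis. What is at stake is how clearly the enrolment stop is fixed. Power is not at risk, as the working shows.

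**Working it through.** **Inputs, all from section {14}:** p1 = 0.555 (early), p2 = 0.339 (delayed), two-sided α = 0.05 (z = 1.960), power 80% (z = 0.842), equal arms, 5% losses.

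Derived quantities:
- difference: 0.555 − 0.339 = 0.216, squared 0.046656
- mean proportion: (0.555 + 0.339)/2 = 0.447
- pooled variance term: 2 × 0.447 × 0.553 = 0.4944
- unpooled variance term: 0.555 × 0.445 + 0.339 × 0.661 = 0.4711

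**Step 1. Reproduce section {14}.** Usual formula, with pooled variance under the null and unpooled under the alternative:

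n = [1.960 × √0.4944 + 0.842 × √0.4711]² / 0.046656 = 81.98, so 82 per arm.

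Losses: 82/0.95 = 86.3, so 87 per arm and **174** in total. Multiplying instead (82 × 1.05 = 86.1) also gives 87. This matches section {14} exactly.

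**Step 2. Can the same inputs give 178?** With pooled variance in both terms:

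n = (1.960 + 0.842)² × 0.4944 / 0.046656 = 83.17, so 84 per arm.

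Losses: 84/0.95 = 88.4, so 89 per arm and **178** in total. Multiplying (84 × 1.05 = 88.2) also gives 89. The result depends on rounding up before inflating: 83.17/0.95 = 87.5 gives 88 per arm and 176.

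**Step 3. Other variants, two-sided with 5% losses.**

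| Formula | n per arm | Total, rounded before inflation | Total, inflated unrounded |
|---|---|---|---|
| Pooled null, unpooled alternative | 81.98 | 174 | 174 |
| Pooled in both terms | 83.17 | 178 | 176 |
| Unpooled | 79.24 | 170 | 168 |
| Arcsine | 81.80 | 174 | 174 |
| Continuity-corrected | 91.00 | 194 | 192 |

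Among these, only pooled variance in both terms gives 178. The Step 1 formula reaches 178 if losses are taken as 7% (82/0.93 = 88.2, so 89 per arm), but section {14} states 5%. Complete blocks of 8 (sections {16a} to {16c}) do not explain it: 174/8 = 21.75 and 178/8 = 22.25, and the full-block total between them is 176.

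**Step 4. Size of the difference.** 178 − 174 = 4 patients, and 4/174 = 2.3%. Power with the Step 1 formula after 5% losses:
- 174: 87 × 0.95 = 82.65 per arm, power 80.3%
- 178: 89 × 0.95 = 84.55 per arm, power 81.2%

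**Step 5. The interim point, if read as a share of the planned total.** 0.70 × 174 = 121.8, about 122. 0.70 × 178 = 124.6, about 125. The difference is 3 patients.

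**The case against.** The strongest defence is that this is an editorial slip with almost no consequence. Section {14} carries the derivation and is the natural operative source, while the Abstract is a summary. Both totals exceed the planned 80% power after losses. That stands, and it is why the point is minor. It does not remove the contradiction, because the article never says that section {14} governs.

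A reader might go further in three directions that the document does not support.

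- **That 178 cannot come from the stated inputs.** It can, as Step 2 shows. Nothing shows that the authors calculated it that way, but 178 cannot be called underivable. What can be said is that section {14} reports 87 per group, which is the result of the usual formula.
- **That the mismatch is what leaves the interim look unfixed.** The look is loose mainly because it is optional and tied to the sample recruited, with no count. It would be just as loose with one total throughout.
- **That the team could exploit the gap after seeing results.** Nothing suggests this is planned. The primary outcome is assessed at 90 ± 14 days by a blinded neurologist. At about 7 patients a month (70 over roughly ten months), 4 more patients take under three weeks, so many recent patients would have no primary outcome when enrolment reached 174. Even in a worst case, testing complete data at both 174 and 178 and claiming success at either, the type I error would be about 5.7% against 5% (normal approximation, correlation √(174/178)).

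**Conclusion.** The contradiction is real and minor. The article gives two totals for one target. The one with a derivation, 174, reproduces exactly from the stated inputs. The other, 178, needs a different variance formula and does not match the per-group figure in section {14}. The cost is 4 patients (2.3%), about 1 percentage point of power, and about 3 patients at a 70% look.

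This rests on the section {14} inputs as stated and on normal-approximation formulas. That 174 is the intended target is an inference from its having a derivation; the article does not say so.

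**What to change.** State one total throughout. The simplest correction is to keep 174 (87 per arm) as in section {14} and change the Abstract. If 178 is the real target, change section {14} to 89 per arm and state the calculation behind it, including the variance formula or any different loss rate.

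Whichever total is kept, express the 70% point in sections {14} and {21b} as a patient count of the planned total: 122 of 174, or 125 of 178. This tightens the interim wording, which would need it even without the mismatch.

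The cost is a short correction to the article, with no change to design, conduct or data collection. With 70 patients randomised at February 2024, enrolment was then below both possible interim counts and both totals. A correction made before those counts are reached could not be taken as driven by results.

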**Discussion:**

This will be the first trial to compare the effect of mechanical ventilation duration (early vs delayed extubation) after satisfactory endovascular thrombectomy for acute ischemic stroke under general anesthesia.

**Trial registration:**

The study protocol was approved April 11, 2023, by the by the Santiago-Lugo Research Ethics Committee (CEI-SL), number 2023/127, and was registered into the clinicaltrials.gov clinical trials registry with No. NCT05847309. Informed consent is required. Participant recruitment begins on April 18, 2023. The results will be submitted for publication in a peer-reviewed journal and presented at one or more scientific conferences.

**Supplementary Information:**

The online version contains supplementary material available at 10.1186/s13063-024-08181-y.

## Introduction

### Background and rationale {6a}

Endovascular thrombectomy in addition to the medical treatment is, in this moment, the standard of care for patients who had a stroke caused by a large vessel occlusion in the anterior circulation [1–6]. Several factors have been described that may influence the evolution and functional status at 3 months of patients who have suffered a stroke and have received endovascular thrombectomy, such as the time between the onset of symptoms and admission to the ward for performing the procedure, adequate control of blood pressure, the size of the cerebral infarct, a worse neurological examination at the time of the procedure, or the type of anesthesia (sedation versus general anesthesia).

Until a few years ago, sedation was recommended over general anesthesia during endovascular thrombectomy for acute ischemic stroke. Recent meta-analyses and randomized studies have shown that general anesthesia with mechanical ventilation is associated with better functional status at 3 months compared to local anesthesia and sedation [7–15], and they recommend its use. But once the procedure is completed, when is the optimal moment of extubation? Currently, there are no guidelines recommending the optimal moment for extubation after endovascular thrombectomy of the patient with stroke under general anesthesia. Prolonged mechanical ventilation time could potentially be linked to increased complications such as pneumonia or disturbances in cerebral blood flow due to the vasodilatation produced by most anesthetic drugs. However, premature extubation in a patient who has suffered a stroke could led to complications such as agitation, disorientation, abolished reflexes, sudden fluctuations in blood pressure, alterations in cerebral blood flow, respiratory distress, bronchial aspiration, and the need for reintubation [16–19].

In two observational studies, authors observed that mechanical ventilation times exceeding 24 h were associated with a higher incidence of pneumonia and a worse functional state at 3 months. However, these are observational studies, and the timing of extubation may have been influenced by other factors such as the size and location of the infarct, the NIHSS (National Institutes of Health Stroke Scale), or the neurological status prior to endotracheal intubation. Therefore, it is challenging to establish a direct relationship between extubation timing and functional prognosis at 3 months in an observational study. Consequently, there is a need for a trial determining whether early extubation (< 6 h) compared to delayed extubation (6–12 h) can influence the evolution and functional status at 3 months of patients who have suffered a stroke and have received satisfactory endovascular thrombectomy under general anesthesia.

We therefore designed a randomized study hypothesizing that early compared with delayed extubation is associated with a better functional outcome, according to the modified Rankin scale, 90 days after endovascular thrombectomy under general anesthesia for acute ischemic stroke.

### Objectives {7}

#### Primary objective

The aim of this prospective randomized study is to compare the effect of early (< 6 h) versus delayed (6–12 h) extubation on functional outcome at 90 days, as measured by the modified Rankin scale (mRS), in patients with acute ischemic stroke treated with endovascular thrombectomy under general anesthesia. The mRS is a categorical scale ranging from 0 (no symptoms) to 6 (death), and it will be assessed by trained research staff blinded to the randomization. Success will be considered as an mRS score of 0–2.

#### Secondary objectives

The study will also investigate the effect of early (< 6 h) vs delayed (6–12 h) extubation after endovascular thrombectomy under general anesthesia for acute ischemic stroke, examining additional outcomes: the percentage of patients unable to be extubated in the assigned group, NIHSS scores on days 1 and 2, time to hospital discharge, mRS scores at hospital discharge, complications during ICU and hospital stay, and lengths of stay in the ICU and Hospital. We aim to identify factors that may influence poorer functional status at hospital discharge (NIHSS and mRS scores) and at 90 days (mRS score).

### Trial design {8}

The EDESTROKE trial is an investigator-initiated, single-center, prospective, parallel, evaluated blinded, superiority, randomized controlled trial.

#### CONSORT diagram

Figure 1 shows the Consolidated Standards of Reporting Trials (CONSORT) diagram of the EDESTROKE trial.

**Fig. 1 Fig1:**
[figure not shown]
The Consolidated Standards of Reporting Trials (CONSORT) diagram of the EDESTROKE trial

## Methods: participants, interventions, and outcomes

### Study setting {9}

The EDESTROKE trial will be conducted in one university Hospital in Spain (University Clinical Hospital of Santiago de Compostela, Galicia, Spain).

### Eligibility criteria {10}

#### Inclusion criteria

Adult (age ≥ 18 years), both genders.Acute ischemic stroke due to large intracranial vessel occlusion demonstrated on CT-angiography in the following anterior circulation locations (occlusion of the internal carotid artery and/or middle cerebral artery in segments M1, M2, M3) within 24 h of symptom onset.Patients admitted with a NIHSS neurological status ≥ 6.Patients who received endovascular treatment under general anesthesia and mechanical ventilation with satisfactory reperfusion (TICI 2b-2c-3).Patients intubated in the interventional radiology room.Patients admitted to the ICU with mechanical ventilation.Written informed consent from the patient or proxy (if present) before inclusion or once possible when patient has been included in a context of emergency.

#### Exclusion criteria

Patients who have not been tracheal intubated in the interventional radiology room.Female subjects with childbearing potential who are pregnant at the time of screeningPatients who suffer bronchial aspiration prior to the endovascular procedure or during tracheal intubation.Patients with pre-existing pulmonary condition potentially requiring ventilatory support.Patients who did not undergo the endovascular procedure under an anesthetic method other than general anesthesia with mechanical ventilation.Patients with functional neurological status, prior to the ischemic stroke, measured with the modified Rankin scale (mRS) of value: 3–6.Patients with vascular involvement of the posterior cerebral circulation, or intracranial hemorrhage associated with stroke.Patients who do not sign the informed consent by themselves or their relatives.

### Who will take informed consent? {26a}

Trial investigators will identify consecutive patients admitted to the ICU with acute ischemic stroke due to a proximal occlusion of the anterior circulation, who meet the inclusion criteria. Eligible patients or their legal representatives if the patient cannot understand information due to an underlying disease will receive written and oral information and will be included in randomization after investigators have obtained informed written consent. Once patients are extubated and if their medical condition allows them to understand the information, they will be given the option to either continue participating in the study or withdraw themselves from it.

### Additional consent provisions for collection and use of participant data and biological specimens {26b}

Not applicable. This trial does not involve collecting biological specimens for storage.

## Interventions

### Explanation for the choice of comparators {6b}

Patients with acute ischemic stroke due to a proximal occlusion of the anterior circulation admitted in ICU after successful endovascular thrombectomy under general anesthesia will be allocated to one of the following two study groups:Early extubation group: patients are extubated < 6 h after endovascular thrombectomy under general anesthesia.Delayed extubation group: patients are extubated 6–12 h after endovascular thrombectomy under general anesthesia.

### Intervention description {11a}

In both groups of patients undergoing endovascular thrombectomy in the interventional radiology room, general anesthesia will be administered at the discretion of the attending anesthesiologist. All patients will be monitored with electrocardiogram, hear rate, pulse oxygen saturation, invasive blood pressure, end-tidal carbon dioxide, inspired oxygen fraction, and blood glucose. Plasma glucose will be maintained within the range of 140–180 mg/dL, and systolic blood pressure will be targeted to be kept between 140 and 180 mmHg, with vasopressor support if necessary. Following endovascular treatment, patients will be transferred to the ICU, and if they meet the inclusion criteria, they will be then randomized into one of two groups: early vs delayed extubation.

In the ICU, patients will be monitored similarly to the interventional radiology room. Because the trial includes patients who have undergone satisfactory endovascular thrombectomy (TICI 2b-3), systolic blood pressure will be targeted to be maintained between 120 and 140 mmHg, with vasopressor support if necessary. Patients allocated to the early extubation group will be extubated within 6 h after endovascular thrombectomy, while those in the delayed extubation group will be extubated between 6 and 12 h after treatment.

During both assigned time frames, patients will be extubated if they meet the following criteria:Hemodynamic stability: The patient should be hemodynamically stable, with blood pressure within acceptable ranges and no significant need for vasopressor support.Respiratory stability: The patient should have adequate respiratory function, with effective mechanical ventilation and no signs of acute respiratory distress.Neurological status: The patient should be awake, alert, and able to follow simple commands. Assessment of airway protection and swallowing capacity will be considered.Assessment of cough and secretion clearance: The patient should have the ability to cough and clear secretions effectively to prevent respiratory complications.Response to spontaneous ventilation: A spontaneous breathing trial may be conducted to assess the patient’s ability to breathe independently without ventilatory support.

If the patient cannot be extubated within assigned time frame for any reason, it will be documented. After extubation, if the patient is clinically stable, they will be transferred to the neurology hospitalization floor and subsequently discharged from the hospital. Ninety days after the endovascular thrombectomy, patients will have a consultation with a neurologist.

### Criteria for discontinuing or modifying allocated interventions {11b}

Patients and their authorized members can withdraw from the study at any time without any negative consequences attached. The study investigators reserve the right to temporarily or permanently halt a patient’s participation in the study if it is deemed to be in the patient’s best interest, particularly in response to a serious adverse event. Affected patients will no longer be subject to protocol monitoring but will continue to receive optimal care based on their health status and current knowledge. In the event of early study withdrawals, the investigator is required to thoroughly document the reasons. Premature termination of the study may occur if unexpected adverse events arise or if unforeseen circumstances or new medical information necessitate sponsor intervention. Any modifications to the study protocol must be documented by the principal investigator. Even in cases of protocol deviation, participant follow-up must continue until the specified endpoint.

### Strategies to improve adherence to interventions {11c}

To improve adherence, patients and their authorized family members will receive comprehensive explanations about the intervention, potential risks, and other details from the recruitment team. They will also be informed about the importance of completing follow-up assessments. They can reach us whenever they have any question or need medical attention.

Except for the extubation timing (early versus delayed extubation), the rest of the treatment in both groups will be provided within the standard of care. Any protocol deviations will be recorded on the electronic case report form, and a clinical research assistant will ensure that all protocol deviations and adverse events are recorded in the database.

